### Outcomes

#### Primary feasibility endpoints

Adequate recruitment (defined as ≥ 15% of eligible patients enrolled per center per month to target consistent levels of enrollment) [33]Adequate cold-stored platelet supply (defined as appropriate product available at the time of surgery for ≥ 90% of patients randomized to the delayed cold-stored platelet group).Adequate clinician adherence to randomization assignment (defined as > 90% of all patients being administered the assigned product).

Recruitment and protocol adherence are key common progression criteria for internal pilots of efficient RCTs and ensuring adequate supply of cold-stored platelets is a critical metric for ensuring feasibility of the definitive trial. If all primary feasibility endpoints are met, we will proceed with the larger trial. If 1–2 of 3 feasibility endpoints are met, we will decide if the trial is feasible with modifications to the protocol addressing the specific deficiencies in trial design identified in the pilot. The trial will be considered infeasible if all primary feasibility endpoints fall short of their targets and can not be addressed with modifications to the study protocol. We will hold an investigator meeting to examine the type and number of major deviations, and to define protocol changes required based on the feasibility outcomes.

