### Determination of sample size

This pilot study will include 50 randomized patients, which, accounting for patients who are randomized but not treated and patients who withdraw in both arms, is expected to provide at least 44 evaluable patients, with 22 in each arm. This sample size of 50 patients allows for sufficiently precise estimates of feasibility outcomes [37] in a reasonable timeline. If fewer than 10% (< 5 patients) receive the incorrect product or receive no product, the upper one-sided 95% confidence limit for this percentage will be ≤ 17.3%. In the 25 patients assigned to cold-stored platelets, if at least 90% have product available, the lower confidence limit will be ≥ 77.7%.

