### Statistical analysis

For the statistical analysis of the efficacy parameters, the following analysis sets will be considered:

The intention to treat (ITT) population: all randomized patients who receive at least a whole or parts of an IMP dose, irrespective of the number of IMP doses received. We anticipate that ≥ 90% of randomized patients will receive the first dose of IMP. Should a patient receive IMP that is not in concordance with the randomization schedule, the treatment group will be defined according to the randomization (rather than the actual treatment received). The primary outcome and mortality for non-consenting patients will be collected from as many sites as possible, as permitted by the local REB.

The per-protocol (PP) population: all patients in the ITT sample, excluding patients with major protocol deviations. Patients meeting any of the following criteria will be excluded.Patients who do not receive at least 80% of the first platelet dose to which they were randomizedPatients receiving treatment not in concordance with the randomization schedulePatients who significantly violate inclusion/exclusion criteria (e.g., did not have cardiac surgery with CPB, randomized after POD-3, etc.)

The restricted safety population (safety analysis set): all patients who receive at least one whole or parts of the first platelet dose (i.e., the ITT population).

A final decision about the classification of protocol deviations as major and minor and their consequences regarding the assignment of patients to analysis populations will be made during the blinded data review meeting prior to unblinding for the final analyses by the lead PI.

The ITT analysis sample is considered the primary sample for analysis of the primary endpoint. The evaluation of the primary endpoint will additionally be performed for the PP sample.

The data will be analyzed using protocols established for safeguarding privacy and confidentiality. These include password-protected computers, locked file cabinets for hardcopies, and no public discussion of individual cases. There will be no linkages to other datasets, and no disclosures of person identifiers. Reports will present aggregate statistics only.

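### The clinician adherence criterion counts non-treatment of any cause, including platelets withheld under the protocol's own treatment criteria, so the dosing level the plan anticipates can miss the target without any clinician non-adherence

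*Protocol article*

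**What the plan says.** All references are to the protocol article.

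- **Primary feasibility endpoints.** Adequate clinician adherence is more than 90% "of all patients being administered the assigned product". Adequate supply is "appropriate product available at the time of surgery for" at least 90% of patients randomized to delayed cold-stored platelets (DCSP).
- **Determination of sample size.** "This pilot study will include 50 randomized patients". The adherence precision statement begins "If fewer than 10% (< 5 patients) receive the incorrect product or receive no product" and gives an upper one-sided 95% limit of at most 17.3%. The section also expects at least 44 evaluable patients, "accounting for patients who are randomized but not treated and patients who withdraw in both arms".
- **Randomization/assignment of interventions.** The envelope is opened when the first platelet order reaches the blood bank, provided both platelet types are available. A list position is not reused if its patient goes untreated.
- **Interventions.** After release, the team gives the platelets only if criteria on bleeding, heparin reversal and platelet count or function are met, with an exception for life-threatening bleeding.
- **Statistical analysis.** The plan anticipates that at least 90% "of randomized patients will receive the first dose of IMP". Point estimates are compared with the targets.
- **Eligibility criteria.** Patients for whom DCSP will not be available at surgery are excluded.

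**The concern.** The label and the scoring measure different things. The label refers to clinicians following the allocation. The scoring counts everyone who did not end up with the assigned product, whatever the reason. Because randomization comes before the check of the treatment criteria, the design itself produces some randomized patients whom the protocol says not to transfuse. Each of them uses up part of the adherence allowance, although the clinician did what was asked.

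The numbers do not fit together either. The dosing rate anticipated in Statistical analysis includes a value, exactly 90%, that the adherence target rejects.

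The criterion is one of three that decide whether the larger trial goes ahead with little or no change. If it is missed for reasons unrelated to clinician behaviour, the trial leaves that branch and the investigators must consider modifications. The Design section makes pooling of the pilot data depend on there being no changes, or only changes not expected to affect the definitive trial's primary endpoints.

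**Working it through.** **Inputs from the protocol article**
- Randomized: 50 in total, 25 assigned to DCSP (Determination of sample size).
- Adherence target: more than 90%, strict (Primary feasibility endpoints).
- Miss: wrong product or no product, fewer than 5 allowed (Determination of sample size).
- Anticipated first-dose receipt: at least 90% (Statistical analysis).
- Supply target: at least 90% of the DCSP arm (Primary feasibility endpoints).

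**1. The plan's own figure.** The one-sided 95% Clopper-Pearson upper limit is the 0.95 quantile of Beta(x + 1, n − x). For x = 4, n = 50, this is 17.38%, which agrees with the stated 17.3% to within 0.1 point. For x = 5 it is 19.9%. The stated limit therefore belongs to 4 misses, which confirms how the rule is read.

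**2. The allowance.** 46/50 = 92% passes; 45/50 = 90% does not exceed 90% and fails. At most 4 misses are allowed, all causes together.

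**3. Against the anticipated dosing rate.** At least 90% of 50 is at least 45 dosed, so up to 5 untreated. Five untreated give 45/50 = 90%, a failed criterion, even if every dosed patient received the assigned product.

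If each patient independently has a true probability of being untreated, and there are no wrong products and no supply failures, then P(pass) = P(Bin(50, p) ≤ 4):

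| True rate untreated | P(pass) |
|---|---|
| 10% (the floor in Statistical analysis) | 0.43 |
| 8% | 0.63 |
| 5% | 0.90 |

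Only the 10% row uses a figure from the document; 8% and 5% are assumed, to show the range.

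**4. Overlap with supply (conditional).** At least 90% of 25 needs 23 (23/25 = 92%; 22/25 = 88% fails), so the supply endpoint tolerates 2 DCSP patients without product. If they were randomized, they received room temperature platelets or nothing, and either is an adherence miss. They use 2 of the 4 allowed. With an assumed 5% rate of other misses:
- no supply failure: P(Bin(50, 0.05) ≤ 4) = 0.90
- two supply failures, scored as written: P(Bin(48, 0.05) ≤ 2) = 0.57
- two supply failures, charged to supply only: more than 90% of 48 allows 4 misses (44/48 = 91.7%), and P(Bin(48, 0.05) ≤ 4) = 0.91

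**5. Precision on a smaller denominator.** With an assumed 44 to 48 patients, more than 90% still allows 4 misses (40/44 = 90.9%; 44/48 = 91.7%). The Clopper-Pearson upper limits for 4 misses are 19.6% (n = 44) and 18.1% (n = 48).

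**The case against.** **Availability is screened before randomization.** Eligibility criteria exclude patients for whom DCSP will not be available, Recruitment has supply confirmed beforehand, and randomization requires both products. If these checks work, a supply failure enters neither endpoint. This stands. A reader might infer that every supply failure is counted twice, or that the 77.7% supply limit shows failures are expected. The documents support neither: a 90% threshold is a tolerance, and 77.7% is a precision statement conditional on meeting it. Double counting needs a failed check or product lost after randomization.

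**The stated rates are floors, not forecasts.** This also stands. Actual dosing may be well above 90%, so 0.43 describes the floor. A reader might also take the 44 evaluable patients as a budget of 6 adherence misses. It is not one: those 6 include withdrawals, and a patient who withdraws after receiving the assigned product is not a miss. The like-for-like figure is 5 untreated against 4 allowed, a gap of one patient at the boundary.

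**Adding the scenarios overstates the risk.** Two supply failures plus 10% untreated among the other 48 gives P(Bin(48, 0.10) ≤ 2) = 0.13. That implies 2 + 4.8 = 6.8 expected misses (13.6%), which is not a pilot running as planned.

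**A second dose that cannot be issued might be called a miss.** The endpoint counts patients, and nothing says that a correct first dose is undone by the second.

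**The consequence is mild.** Missing one endpoint leads to a meeting on the type and number of deviations, where the cause could be seen. This limits the harm. It does not remove the defect, because the pass or fail itself is set by the point estimate.

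None of this answers the main point, that withholding platelets under the Interventions criteria is scored as non-adherence.

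**Conclusion.** The concern holds in a limited form. The adherence criterion mixes clinician behaviour with protocol-compliant non-treatment, and its 4-in-50 allowance is one patient tighter than the non-treatment that the plan's own anticipated rate permits. At that rate's floor the criterion is met with probability 0.43, assuming independent patients and no other misses; at an assumed 5% untreated it is 0.90. The result therefore depends on how often the treatment criteria turn out to be unmet after randomization, a rate the document does not give separately.

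The supply overlap is secondary and arises only if product is missing after randomization despite the checks. If it does, two tolerated failures take half the allowance.

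A reader might conclude that the pilot could be declared infeasible on this ground. The document does not support that: infeasibility requires all three endpoints to fall short without a workable modification. What is at stake is an unnecessary departure from the proceed branch. The stated confidence limit is not in dispute; the endpoint definition is what needs correcting, and it should be fixed before the criterion is applied.

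**What to change.** 1. Score adherence among randomized patients whose assigned product could be issued and for whom the treatment criteria in Interventions were not documented as unmet. Keep the target above 90%.
2. Keep as misses both wrong product and non-administration at the clinician's discretion. Do not restrict the denominator to patients who were transfused: clinicians are blinded and the blood bank selects the product, so non-administration is the main way they can fail to adhere.
3. Charge unavailability after randomization to the supply endpoint only.
4. Report treated/randomized as a separate rate against the 90% anticipated in Statistical analysis, and make the strict and non-strict 90% thresholds agree.
5. Restate the upper limit in Determination of sample size for the new denominator: about 18.1% to 19.6% for 4 misses in 48 to 44 patients, in place of 17.3%.

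The cost is a slightly wider limit and a reason code for each non-administration, assigned without knowledge of allocation where possible. The Blinding section already has the blood bank record why a dose was returned. Sample size and clinical conduct do not change.

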#### Secondary patient-centered outcomes

(i) mean number of allogeneic blood components (ABCs) transfused (including red blood cells, plasma, and platelets) within 24 h of CPB end, with each platelet recorded as 3.5 units based on donor exposure (as 2 buffy coat platelets prepared from 7 donors), (ii) mean number of ABCs within 7 days of CPB, (iii) total number of coagulation factor products administered (fibrinogen concentrate, prothrombin complex concentrates, and activated recombinant factor VII) within 24 h and 7 days of CPB, (iv) incidence of severe to massive bleeding (using a modification of the universal definition of perioperative bleeding [UDPB] in cardiac surgery, and its individual components [34, 35]) within 24 h of CPB, (v) chest tube drainage at 12- and 24-h after chest closure, (vi) total platelet count with a functional platelet count (PlateletWorks) at preoperative baseline, at the time of rewarming on CPB, immediately after CPB at protamine reversal, within 60 min before first product administration, and within 60 min after first product completion, and (vii) changes in international normalized ratio (INR), prothrombin time (PT), activated partial thromboplastic time (aPTT), fibrinogen activity, rotational thromboelastometry (ROTEM) EXTEM clotting time (CT) and maximum clot firmness (MCF), ROTEM FIBTEM MCF and thrombin generation, from within 60 min before to within 60 min after the initiation of the first product administration, (viii) EQ-5D-5L version of EQ-5D™ questionnaire [36] was collected at baseline and at postoperative day (POD) -30, and (ix) case-costing data for each patient.

Additional safety outcomes include (i) incidence of serious treatment-emergent adverse events (AE) from the start of surgery to POD-30, (ii) incidence of thromboembolic events from randomization to POD-30, (iii) duration of ventilation and ventilator-free days up to POD-30, (iv) duration of intensive care unit (ICU) stay up to POD-30, (v) duration of hospitalization up to POD-30, (vi) incidence of death up to POD-30, and (vii) days alive and out of hospital at POD-30.

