**Fig. 1 Fig1:**
[figure not shown]
Study flow

**Table 1 Tab1:** Flow chart of assessments performed throughout the study

Procedures	Before surgery	Surgery	Each platelet administration	POD-1	POD-7 or DC	POD-30
Obtain consent	X					
Inclusion and exclusion criteria	X					
Randomization criteria			x^b^			
Treatment criteria			x			
Platelets stored	X					
Intervention administered			x			
Baseline data						
Demographics	X					
Medical history	X					
Concomitant medications	X					
Surgical data						
Procedure details, date	X					
Intraoperative medications		x				
CPB time		x				
Transfusion data						
Platelets			x	x	x	x
Red cells				x	x	x
Plasma				x	x	x
Hemostatic agents				x	x	
Laboratory assessments						
Complete blood count	X	x	x	x	x	X
Platelet count (total, functioning)	X	x	x			
Coagulation profile ^a^		x	x			
Chemistry	X	x	x	x	x	X
Hematology	X	x	x	x	x	X
Safety labs	X	x	x	x	x	x
Bleeding						
Bleeding severity scale			x			
Chest tube output			x	x		
UDPB				x		
Additional endpoints						
Ventilation time				x	(x)	(x)
Duration of ICU stay				x	(x)	(x)
Hospital length of stay					x	(x)
All-cause mortality				x	(x)	(x)
AEs and SAEs				x	x	x
Treatment-emergent events				x	x	x
Quality of life	X					x
Unblinding			x		x	

*AEs* Adverse events, *CPB* Cardiopulmonary bypass, *DAOH* days alive and out of hospital, *DC* discharge, *ICU* intensive care unit, *POD* postoperative day, *SAEs* serious adverse events, *UDPB* universal definition of perioperative bleeding

() if needed

^a^Activated clotting time, PT, aPTT, INR, fibrinogen activity via Clauss assay, ROTEM EXTEM CT, ROTEM EXTEM MCF, ROTEM FIBTEM MCF, thrombin generation

^b^Only for first platelet administration

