### Randomization/assignment of interventions

Recruited patients will only be randomized on the day of surgery if the clinical team places an order with the blood bank for platelet transfusion to treat active bleeding during the first 6 h after termination of CPB, and both platelet types are available (Fig. 1). When the platelet order is received, the blood bank technologist or assigned research coordinator will confirm the patient has consented to the study and is enrolled in the trial. The patient will then be randomized and the assigned product will be released [18, 24].

Patients will be randomly assigned (1:1 ratio) to study groups on the day of surgery using a permuted block, stratified (by center) allocation scheme prepared by a biostatistician not involved in the trial. Sequentially numbered sealed envelopes based on the randomization lists will be provided to the blood banks that will be providing the platelet product. This process, which has been successfully used in previous similar studies [25–28], has the advantage of allowing the technologists or coordinators to randomize patients as soon as the order is received without delaying therapy. The spot in the randomization list will not be reused if the patient assigned to it does not receive the platelet product. Once the order for the first platelet product is received and eligibility has been confirmed, the blood bank technologist will open the randomization envelope, and prepare and release the assigned platelet product in tamper-proof, temperature-stable containers that have been validated for this purpose and will be identical for each study arm. To maintain blinding, thermal gloves will be released by the blood bank for product handling and the product label (containing collection and expiration dates and type of platelet) will be obscured.

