### Interventions

Patients randomized to the room temperature platelet (RTP) group will receive ABO-identical, pathogen-reduced via INTERCEPT [29], buffy-coat platelets in platelet additive solution maintained at 22 °C for up to 7 days, as per the current standard of care.

Patients randomized to the delayed cold-stored platelet (DCSP) group will receive up to two doses of ABO-identical, pathogen reduced via INTERCEPT, buffy-coat platelets in platelet additive solution maintained at 22 °C for up to 4 days (with agitation) then placed in cold-storage (at 1–6 °C, without agitation) for a minimum of 24 h, with expiration at 14 days after collection.

The duration of treatment is from the initiation of the first platelet transfusion up to 24 h after CPB or receipt of two doses of the product, whichever occurs first. There will be no other changes to participants’ pre-and post-operative management.

The clinical team will then administer the platelets only if the following criteria are met: [23, 30] (a) bleeding is severe enough to necessitate treatment (Bleeding Severity Scale Moderate or higher [31] or chest tube output ≥ 200 mL/h for any 1 h or ≥ 2 mL/kg/h for 2 consecutive hours in the first 6 postoperative hours [32]; (b) heparin is adequately reversed (confirmed by the return of post-protamine activated clotting time [ACT] to within 15% of baseline ACT); and (c) presence of thrombocytopenia (total platelet count < 100,000 × 10^6^) or platelet dysfunction (functioning platelet count < 75,000 × 10^6^ in response to collagen activation, as measured by the point-of-care platelet function assay PlateletWorks currently in use at both sites). Patients can also be treated irrespective of the platelet count or function if bleeding is deemed to be life-threatening, in accordance with institutional coagulation management algorithms for massive bleeding previously validated by our group [23]. Once the decision is made to administer platelets, the administering clinician will put on the insulated gloves provided, retrieve the product from its sealed temperature-controlled container, carry out routine checks, and administer according to usual care including in-line filtration tubing (170–260 µm) primed with normal saline.

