The planned primary outcome for the definitive study will be the mean number of ABCs transfused (including red cells, plasma, and platelets) within 24 h of CPB end. This outcome is an accepted measure of hemostatic efficacy that captures clinically relevant differences between study arms. It has been used as a primary outcome in a large randomized controlled trial comparing fibrinogen concentrate to cryoprecipitate in cardiac surgical patients in Canada [26, 28]. This outcome was used to support Canadian regulatory approval of fibrinogen concentrate in cardiac surgical patients, demonstrating its validity and importance for key regulatory stakeholders, and was a recommended outcome from the recent NHLBI Hemostasis Clinical Trial Outcomes Working Group [41].

Patient management in the control group will reflect current practice and patient management in the intervention group will reflect how delayed cold-stored platelets will be used in practice. For these reasons, the definitive study will have good external validity.

Blood suppliers have indicated an urgent need for innovative platelet storage modalities to extend platelet lifespan without compromising efficacy or safety, a problem delayed cold-stored platelets may be able to address [24, 42]. A well-designed, multicentre RCT is required to assess the comparative efficacy and safety of cold-stored and room-temperature buffy-coat prepared platelets. If the results of the definitive RCT are positive, they will be used to support future licensing by CBS, Canada’s main blood supplier of this product in Canada. Moreover, because buffy-coat prepared platelets are the “industry standard”, findings of such a trial will also be applicable to most other countries, including the UK, Europe, Australia, and most of South America. Buffy coat, and pooled, pathogen-reduced platelets by INTERCEPT are the most common platelet products currently utilized worldwide. If this trial has a positive or non-inferior result, it may result in platelets being able to be stored near operating rooms in controlled fridges for near-patient access, and due to their longer shelf life, the feasibility of stocking smaller hospitals without platelet shakers and with lower transfusion volumes may be increased. The proposed pilot study is designed to determine optimal trial procedures, including the provision of delayed cold-stored platelets at participating hospitals, for the definitive trial.

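### The 24-h blood-product count and the chest drainage outcome start before randomisation or first dose, which costs precision but does not bias a difference in means

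*Protocol article*

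**What the plan says.** Time zero is set in the Protocol article under Randomization/assignment of interventions. A consented patient is randomised only when the treating staff "places an order with the blood bank for platelet transfusion to treat active bleeding during the first 6 h after termination of CPB". Stock of each study product must also be on hand. The envelope is opened when the first order arrives.

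The two hemostatic outcomes run on other clocks:

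- Outcome (i), under Secondary patient-centered outcomes, is the mean number of ABCs "transfused (including red blood cells, plasma, and platelets) within 24 h of CPB end". The Discussion carries it forward: "The planned primary outcome for the definitive study will be the mean number of ABCs transfused", again within 24 h of CPB end.
- Outcome (v), in the same list, is "chest tube drainage at 12- and 24-h after chest closure".

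Under Interventions, one of the bleeding criteria for giving the released product is "chest tube output ≥ 200 mL/h for any 1 h or ≥ 2 mL/kg/h for 2 consecutive hours in the first 6 postoperative hours". The alternative criterion is at least moderate bleeding on the Bleeding Severity Scale, which needs no chest tube.

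Table 1 schedules "Chest tube output" at each platelet administration and on POD-1. Red cells and plasma are first listed at POD-1. Under Outcome assessment, everything except the quality-of-life questionnaire is taken from the electronic medical record. Nothing in the article subtracts, or adjusts for, what was transfused before randomisation or drained before the first dose.

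**The concern.** An outcome meant to show what the platelet product does should cover time in which the product could act. Both measures open earlier. Red cells and plasma given between CPB end and the platelet order are scored as outcome although allocation did not yet exist. For a patient who qualifies on chest tube output, the qualifying bleed is itself part of the 12-h and 24-h readings. A patient whose first dose is given before the chest is closed has no such component, so the drainage reading has a different make-up from patient to patient.

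The same article ties other outcomes to randomisation or to the product: thromboembolic events run from randomisation, and the coagulation changes are measured around the first administration.

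Precision is at stake, mainly in the definitive trial. The pilot plans no formal inference on these outcomes, but its data are to enter the definitive dataset. The Design section makes that conditional on protocol changes not being expected to affect the definitive primary endpoint. The outcome window is therefore easier to settle now than after the pilot.

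**Working it through.** The article gives no figure on this point, so there is none to reproduce. The check compares each outcome clock with time zero.

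**1. ABC count.** Let t be the hours from CPB end to the first platelet order, with 0 ≤ t ≤ 6. The share of the 24-h window before randomisation is t/24.

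| t (h) | share before randomisation | hours left after randomisation |
|---|---|---|
| 0 | 0% | 24 |
| 1 | 1/24 = 4% | 23 |
| 3 | 3/24 = 12.5% | 21 |
| 6 | 6/24 = 25% | 18 |

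These are shares of time, not of products. The first platelet order after CPB triggers randomisation, so the platelet part of the count (3.5 units per platelet) falls essentially all afterwards. Only red cells and plasma can fall before it.

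**2. Drainage, minimum carried in.** This applies to a patient who receives the first dose after closure on the chest-tube criterion:

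- 1-h rule: 200 mL/h × 1 h = at least 200 mL.
- 2-h rule: 2 mL/kg/h × 2 h = at least 4 mL/kg.

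The criterion refers to the first 6 postoperative hours, which lie inside both the 12-h and the 24-h windows, so the amount enters both readings. For a first dose before closure the carried-in amount is zero.

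**3. Drainage, time share.** Let c be the hours from CPB end to chest closure. The article gives no value; I assume 0.5 to 2 h. Hours of the drainage window before the order = max(0, t − c). At the latest order, t = 6:

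- c = 2: 4 h, which is 4/12 = 33% of the 12-h window and 4/24 = 17% of the 24-h window.
- c = 0.5: 5.5 h, which is 5.5/12 = 46% and 5.5/24 = 23%.

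If the order comes before closure, the share is zero.

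**4. Effect on the comparison.** Write each patient's outcome as Y = A + B, with A the part before randomisation (or first dose) and B the part after. Let m be the mean of A, equal in expectation in both arms, and let b₁ and b₀ be the arm means of B.

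- Difference in means: (m + b₁) − (m + b₀) = b₁ − b₀. A cancels, so there is no bias.
- Ratio: (m + b₁)/(m + b₀) is closer to 1 than b₁/b₀ whenever m > 0. Shrinkage arises only on this scale.
- Variance: Var(Y)/Var(B) = 1 + k² + 2ρk, where k = SD(A)/SD(B) and ρ is their correlation.

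Neither k nor ρ is in the article. Purely as an assumed illustration, k = 0.25 with ρ = 0 gives 1 + 0.0625 = 1.06, and k = 0.5 with ρ = 0.5 gives 1 + 0.25 + 0.5 = 1.75. The width of that range shows that the loss cannot be pinned down from the article.

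**The case against.** The case for leaving the outcomes alone is substantial:

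- **No bias on the planned scale.** The Statistical analysis section estimates differences in means or percentages between arms, and the planned definitive primary is a mean. On a difference in means the early part cancels. This stands.
- **Drainage may concern few patients.** Statistical considerations describes the decision to give platelets as intraoperative, and the Bleeding Severity Scale is a separate route to treatment. This stands; the article gives no split.
- **The 200 mL is certain only before the dose.** The criteria under Interventions govern administration, which follows the order and randomisation. The qualifying drainage normally precedes randomisation too, but not necessarily. This stands, and is why drainage is referred to the first dose here.
- **The CPB-end clock is reasoned.** It ends with the treatment period, and the Discussion supports the ABC outcome by its use in an earlier trial and by regulators. This is a good reason to keep reporting that count, but not a reason to leave the early part unadjusted.
- **Low stakes in the pilot.** These are secondary outcomes, and progression rests on three feasibility endpoints. This is true of the pilot, but the ABC count becomes the definitive primary and pilot data are to be reused.

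A reader might also infer more than the article supports:

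- *That the early part pulls the definitive trial towards a false non-inferiority conclusion.* That needs a ratio or percentage scale, and the article fixes neither such a scale nor a margin. On a difference in means, extra variance widens the interval and makes non-inferiority harder to show.
- *That patients whose chest is left open would score low on drainage although they bled most.* The article does not mention delayed closure or its frequency, and such bleeding would still be reflected in the ABC count and the perioperative bleeding definition.
- *That a specific gain in effective sample size can be quoted.* That needs an assumed variance share for the early products and their covariance with later ones; the article gives neither.

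**Conclusion.** The point holds as a matter of precision and clean definition. As worded, the ABC count can include red cells and plasma from an interval of 0 to 6 h, or 0 to 25% of its window, before randomisation. In patients treated after closure on the chest-tube criterion, the drainage readings include at least 200 mL or 4 mL/kg from before the first dose. Both statements follow from the article's own definitions.

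The consequence is added variance, not bias in a difference in means; a contrast would shrink only on a ratio or percentage scale. How many patients are affected and how much precision is lost cannot be derived from the article. The closure times and variance ratios used in the check are assumptions that only illustrate the mechanism. This is a cheap improvement, best made before pilot data pass into the definitive dataset.

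**What to change.** **Outcome (i).** Analyse ABCs from randomisation to 24 h after CPB, and report the count from CPB end alongside it for comparability with earlier trials. Follow-up then varies from 18 to 24 h between patients, but in the same way in both arms by randomisation. Alternatively, keep the CPB-end count and adjust for products given between CPB end and randomisation.

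**Outcome (v).** Keep the readings at 12 and 24 h after chest closure. Adjust for, or subtract, cumulative chest tube output before the first study dose, taken as zero when that dose precedes closure. Confirm that the chest tube output scheduled in Table 1 at platelet administration is recorded as a cumulative volume; an hourly rate could not be subtracted.

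**Cost.** One extra tabulation, and use of time-stamped transfusion and drainage entries from the electronic record. Time stamps matter because Table 1 first lists red cells and plasma at POD-1, and the article does not say that the time of randomisation is recorded; the data form should capture it. Nothing in treatment or eligibility changes.
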